## Methods/design

This single-blind, two-arm, parallel-group, randomized controlled trial comprises an intensive longitudinal design with three end-of-day diary periods: A *baseline diary* (3 consecutive days), a *challenge diary* from 7 days before the self-set quit date, on the self-set quit date until 20 days after the self-set quit date (28 consecutive days) and a *follow-up diary* 6 months after the self-set quit date (3 consecutive days). See Fig. 1 for the longitudinal design.

**Fig. 1 Fig1:**
[figure not shown]
The longitudinal study design

Participants of this randomized controlled trial are adult smokers, who smoke at least one cigarette daily [43], intend to quit smoking during the study, and own a smartphone with access to mobile internet. Moreover, participants should speak German fluently, should not work in 24-h shifts, should not participate in a professional smoking cessation program, and should not already use a smoking cessation smartphone app. Recruitment takes place in Switzerland and is organized via advertisements in newspapers, online platforms and on webpages, flyers and postings in the university, medical facilities and local companies. Interested individuals can complete a prescreening assessment online, for which they provide informed consent and that checks inclusion and exclusion criteria. In case smokers meet all inclusion criteria, they are contacted via email and sent the link for an online end-of-day diary questionnaire for three consecutive days (baseline diary).

After completing the baseline diary participants are contacted and invited to the lab for a background assessment. At the background assessment participants first receive full information on the study, and provide written informed consent. After completing a comprehensive background questionnaire, participants are asked to set a self-set quit date within the next 6 weeks. They are instructed to fill in the online challenge diary from 7 days before the self-set quit date, on the self-set quit date and 20 days after the self-set quit date. During those 28 days all participants receive a daily text message with the link for the questionnaire at seven o’clock in the evening. Subsequently, participants receive an instruction for the personal mobile objective smoking abstinence measure, the iCO Smokerlyzer (Bedfont Scientific Ltd.), and the corresponding smartphone app to measure the exhaled carbon monoxide (CO) daily. A first measurement of CO with the iCO Smokerlyzer is already taken in the lab. Lastly, participants of the intervention group are introduced to the smartphone app (for details on randomization procedure and the intervention see below). Six months after the self-set quit date, participants of both groups are contacted via email and asked to participate in the follow-up diary phase for completing online end-of-day diaries for three consecutive days and daily objective assessments of smoking with the iCO Smokerlyzer.

As a main incentive for study participation, all participants will receive the iCO Smokerlyzer a carbon monoxide monitor for the smartphone, with a value of 60 CHF (= 63 USD). Additionally, with completion of the six-month follow-up, participants from both groups are given entry into a lottery. The lottery has one main prize of 200 CHF (= 209 USD), and 40 prizes with a value of a 50 CHF (= 52 USD) shopping vouchers. Participants in the role of the supporting buddy will be reimbursed with 50 CHF (= 52 USD) with completion of the study.

### Randomization

The randomization comprises a random assignment to one of the two groups (intervention group and control group). Blocking as means of restricted randomization is used: To meet balance and predictability criteria [44, 45] variable blocks (4, 6, 8) are used. Within a block of participants, 50% are assigned to the intervention group and the control group. Before the beginning of the study, a computerized random-number generator (http://www.randomization.com) is used for sequence generation of blocks. This allocation sequence is generated by an assistant not part of the study team and to ensure allocation concealment concealed in a set of sealed, numbered envelopes until group assignment. On the day of the background assessment in the lab, the interviewer conducting the session opens the appropriate numbered envelope and prepares the study material accordingly. Throughout the study, participants are blinded to the group assignment (i.e., single-blind RCT).

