#### Intervention group: SmokeFree buddy app group

In addition to the instructions of the daily assessments with the iCO Smokerlyzer, target persons of the intervention group will be introduced to the SmokeFree Buddy app and instructed on how to use it during the challenge diary phase (7 days before the self-set quit date, on the self-set quit date until 20 days after the self-set quit date). The SmokeFree Buddy app is a smartphone app that aims at enabling smokers to quit with the help of a self-chosen buddy from one’s social network and offers the possibility of enhancing social support resources and availability directly after a self-set quit attempt in smoker’s everyday life.

Participants of the intervention group have to identify a personal buddy (self-chosen from their personal social network) with whom they will start the smokefree challenge. The smartphone app has a scientific background, and was developed by the Federal Institute of Health in Switzerland in collaboration with the Institut de Santé Globale of the University of Geneva in Switzerland. For more details about the SmokeFree Buddy app please see https://www.smokefree.ch/en/buddy-app/. For an overview of the most prominent BCTs of the SmokeFree Buddy app, please see Table 1.

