#### Control group

The participants in the control group will also announce a self-set quit date, measure the exhaled carbon monoxide daily using the iCO Smokerlyzer and fill out the end-of-day diary for 28 consecutive days during the diary phase. Smokers in the control group will, thus, have the same setting as the intervention group only without the SmokeFree Buddy app.

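### The trial is described as single-blind with participants unaware of their group, but its own procedures show every participant whether they received the app

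*Protocol article*

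**What the plan says.** The protocol article makes the blinding claim in three places. The abstract (Methods) uses the single-blind label. Methods/design opens with "This single-blind, two-arm, parallel-group, randomized controlled trial comprises an intensive longitudinal design with three end-of-day diary periods". The Randomization section spells out what is meant: "Throughout the study, participants are blinded to the group assignment (i.e., single-blind RCT".

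The procedures are these:

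- **Information and consent (Methods/design, text after Fig. 1):** "At the background assessment participants first receive full information on the study, and provide written informed consent".
- **Intervention arm:** "target persons of the intervention group will be introduced to the SmokeFree Buddy app and instructed on how to use it". In addition, "Participants of the intervention group have to identify a personal buddy (self-chosen from their personal social network"), and the two then communicate through the app during the quit attempt.
- **Control arm:** smokers "have the same setting as the intervention group only without the SmokeFree Buddy app".
- **Diaries (Measures):** controls receive no buddy items, and intervention smokers also report on their use of the app.
- **Allocation (Randomization):** on the day of the background assessment "the interviewer conducting the session opens the appropriate numbered envelope and prepares the study material accordingly".

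The aims section names two primary outcomes, daily self-reported abstinence and daily abstinence by exhaled CO, and one secondary outcome, the self-reported number of cigarettes. It states no precedence between the two primary outcomes.

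**The concern.** This is a positive statement that the rest of the document contradicts. It is not a detail left to a fuller protocol or to the analysis plan. A participant who has been informed about the study, and who then either is or is not given an app and told to find a buddy, can tell which of the two happened.

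Two things are at stake. First, a false single-blind label would pass into reports and risk-of-bias ratings as a protection the trial does not have. Second, the label bears on outcomes that participants report themselves. Pressure to report abstinence may differ by arm: only intervention smokers have a buddy who is notified of cravings and lapses, and Table 1 lists social reward and monitoring by others for that arm alone. The Discussion argues that the effect of daily self-report and CO measurement is constant across arms. That deals with reactivity to being monitored, not with differential reporting by people who know their arm.

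A smaller, related point concerns the lab visit. The Randomization section does not say at which step the envelope is opened. The self-set quit date, chosen during that visit, anchors every outcome time point.

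**Working it through.** **1. Can the blinding statement be true?**

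| Feature | Intervention arm | Control arm |
|---|---|---|
| Study information before consent | Full | Full |
| Quit date, diary, CO device | Yes | Yes |
| Buddy app | Introduced and instructed | None; no sham described |
| Buddy | Must be found by the participant | None |
| Diary items on buddy and app use | Yes | No |

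The last three rows are visible to the participant and differ by arm. The text claims blinding to group assignment, so these rows are enough to contradict it. The interviewer opens the envelope and so knows the arm from that moment. No other role is described as blinded. The document says nothing about analysts.

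**2. Does blinding enter the sample size?** Inputs from Power analysis: control abstinence 27%, difference 24 points (hence 51%), two-sided alpha 0.05, power 0.80. With pooled variance and mean proportion 0.39:

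n per arm = [1.960·√(2·0.39·0.61) + 0.842·√(0.27·0.73 + 0.51·0.49)]² / 0.24² = 63.6, rounded up to 64, or 128 in total.

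This reproduces the stated N = 128 (power at 64 per arm: 0.802). No input depends on blinding, so correcting the label leaves N unchanged.

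**3. What could differential reporting do?** The documents give no misreporting rate, so this step is an assumption shown as a range. Let true abstinence be 27% in both arms. Let an excess share m of app-arm smokers, relative to controls, falsely report abstinence. The observed app-arm rate is p₂ = 0.27 + 0.73·m. The rejection rate is that of a pooled two-proportion z-test at two-sided 5%:

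P(reject) = 1 − Φ[(1.96·SE₀ − d)/SE₁] + Φ[(−1.96·SE₀ − d)/SE₁]

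Here d = p₂ − 0.27, SE₀ uses the pooled proportion, and SE₁ uses the two separate proportions.

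Worked case, m = 10%, 80 per arm: p₂ = 0.27 + 0.073 = 0.343; d = 0.073; SE₀ = √(2·0.3065·0.6935/80) = 0.0729; SE₁ = √((0.1971 + 0.2254)/80) = 0.0727. The rejection rate is about 17%.

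| Excess over-reporting m | Shift in self-report | Rejection, 64 per arm | Rejection, 80 per arm |
|---|---|---|---|
| 0% | 0 | 5.0% | 5.0% |
| 2% | 1.5 points | 5.4% | 5.5% |
| 5% | 3.7 points | 7.4% | 8.0% |
| 10% | 7.3 points | 14.5% | 17% |
| 15% | 11.0 points | 26% | 31% |

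**4. Effect of the dropout rule.** Statistical analysis treats participants who drop out completely as smokers, so they cannot over-report. Assume the 25% attrition from Power analysis lies wholly within the 73% who are not abstinent. Then 73% − 25% = 48% can over-report. At m = 10% the shift is 0.48·0.10 = 4.8 points, and rejection at 80 per arm is about 10% rather than 17%.

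**The case against.** The strongest reply is that the error is one of labelling and that the design already contains the remedy. CO is measured daily in both arms, is itself a primary outcome, and can be compared with self-report day by day. Participants enter their diary outcomes online, so the interviewer does not rate them. Controls also receive an active package (quit date, diary, and a CO monitor with its own smartphone app) and might not realise that theirs is the comparison arm. What was disclosed about the two arms is not shown.

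Much of this stands. The CO outcome is far less exposed, though readings are self-taken and can be omitted. Participants may be unaware of the hypothesis. But the text claims something else, blinding to group assignment, and none of this makes that claim true.

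Four stronger readings are tempting and are not supported:

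- **Nobody in the trial is blinded.** The document is silent on analysts, so this is not shown.
- **The interviewer knows the arm during consent and quit-date setting.** Methods/design puts the app introduction last, and Randomization keeps the sequence sealed until assignment. Early knowledge is possible only because the moment of opening is not fixed.
- **The false-positive rate is 17%.** That is one assumed scenario, computed with a simple test rather than the planned mixed logistic model. If controls over-report at 5% and the app arm at 10%, rejection at 80 per arm is 7.8%.
- **Self-report must lose its primary status.** The trial was prospectively registered, and the ranking of outcomes does not follow from a wording error.

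**Conclusion.** The claim that participants are blinded to group assignment is wrong as written. Participants know whether they received the app, and the interviewer knows the arm once the envelope is open. Self-reported abstinence and cigarette counts therefore come from unblinded participants, and a self-report difference alone supports less than the label suggests.

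The documents establish exposure to reporting bias, not its direction or amount. Under the stated assumptions (no true effect, 27% abstinence, 2% to 15% excess over-reporting in the app arm, simple two-proportion test), the false-positive rate at 80 per arm runs from about 5.5% to 31%, and lower once dropouts are counted as smokers. The point should be corrected. It does not undermine the randomisation, the CO outcome or the sample size.

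**What to change.** - Remove the single-blind label in the abstract, Methods/design and Randomization. State that participants and the interviewer are not blinded, and name any role that is.
- Acknowledge that self-reported abstinence and cigarette counts come from unblinded participants. State that any self-report effect will be interpreted against the daily CO-based primary outcome. Giving CO formal precedence is a reasonable option, but it is the sponsor's choice.
- State that the envelope is opened only after consent, the background questionnaire, the quit date and the lab CO reading have been recorded.

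The first two items cost wording only. The third costs wording and, if current practice differs, a reordering of steps within one existing visit. If the sponsor chose to give CO precedence, that would change the registered outcome hierarchy and would need to be documented as such.

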### Detailed description of intervention procedure and control group

This study has an EMI design [40] and comprises two groups: a SmokeFree Buddy app intervention group and a control group (see below). As described above, at the background assessment all participants are instructed to set a self-set quit date, to fill out the end-of-day diaries for 28 consecutive days and to measure the exhaled carbon monoxide daily during the challenge diary phase using the iCO Smokerlyzer. Setting a self-set quit date comprises the BCT “goal setting of behavior” [25]. The daily CO measure comprises the BCT “feedback on behavior” and “self-monitoring of behavior” [25]. For an overview of the most prominent BCTs included in the study please see Table 1.

**Table 1 Tab1:** Overview of intervention components and corresponding most prominent BCTs in intervention group (IG) and control group (CG)

Groups	Intervention components	Behavior change techniques (BCTs)
IG + CG	Set a self-set quit date	Goal setting of behavior
IG + CG	Daily CO measure and end-of-day diary across 28 days	Feedback on behavior
		Self-monitoring of behavior
IG only	The SmokeFree Buddy app	Social support (emotional), social support (practical)
		Social reward
		Feedback on behavior
		Self-monitoring of behavior, others monitoring with awareness
		Discrepancy between current behavior and goal standard
		Non-specific reward
		Information about health consequences

*IG* Intervention Group, *CG* Control Group

#### Intervention group: SmokeFree buddy app group

In addition to the instructions of the daily assessments with the iCO Smokerlyzer, target persons of the intervention group will be introduced to the SmokeFree Buddy app and instructed on how to use it during the challenge diary phase (7 days before the self-set quit date, on the self-set quit date until 20 days after the self-set quit date). The SmokeFree Buddy app is a smartphone app that aims at enabling smokers to quit with the help of a self-chosen buddy from one’s social network and offers the possibility of enhancing social support resources and availability directly after a self-set quit attempt in smoker’s everyday life.

Participants of the intervention group have to identify a personal buddy (self-chosen from their personal social network) with whom they will start the smokefree challenge. The smartphone app has a scientific background, and was developed by the Federal Institute of Health in Switzerland in collaboration with the Institut de Santé Globale of the University of Geneva in Switzerland. For more details about the SmokeFree Buddy app please see https://www.smokefree.ch/en/buddy-app/. For an overview of the most prominent BCTs of the SmokeFree Buddy app, please see Table 1.

The SmokeFree Buddy app has the following features: (1) Buddy support. The main feature of the app is a chat function through which the smoker and the personal buddy are connected. The chat is the app’s direct communication channel for all text-messages between the smoker and the buddy. Apart from the text-messages sent, the chat lists all events occurring within the app (e.g. notifications, mood change, bonuses; see below). The app informs the buddy for example about the smoker’s current mood or craving and provides them with the option of reacting immediately, e.g. with a supportive message. The buddy can choose one of many preset messages, which can be customized or supplemented with a personal comment. Unlike anonymous computerized notifications, support through the SmokeFree Buddy app is personal, from a buddy and can be tailored to the smoker’s need. (2) Current mood and notification buttons. The app provides a feature to indicate the current mood state and intensity of the smoker (e.g. joy, depressed, anger) that is also visible for the buddy. Additionally, there are three different notification buttons on the smoker’s side: SOS! (sending an emergency message), desire (communicating an urge/craving to smoke, from 1 [= slight] to 5 [= strong]), and lapse (number of cigarettes smoked). A change in mood or a click on one of the notification buttons directly sends a message to the buddy (via chat), requesting their support as soon as possible. The app provides background information of these different situations and preset messages for the buddy, which can be personalized. (3) Bonuses. With the bonus-feature the buddy can motivate the smoker. Various bonuses are available such as encouraging, confirmation of success or advice for a particular challenge. In the bonus gallery the target persons are able to see the trophies that they have earned any time. (4) Performance statistics. These statistics show the target person’s achievement to date: The number of smoke-free days, the number of cigarettes that the smoker did not smoke (i.e. being smoke-free) and the amount of money he or she was able to save. (5) Knowledge base. A Knowledge base allows smoker and buddy to rapidly retrieve information on smoking and quitting and share it with each other via the chat. There is also a permanent information bar that shows health benefits of stopping smoking over the course of time. Moreover, the app provides contact information to a quit helpline and professional smoking cessation counseling.

After being introduced to the app, participants of the intervention group are instructed to find a buddy with whom they will communicate through the app during their self-set quit attempt. The buddy has to be a non-smoker for at least 6 months [46]. Furthermore, they should also own a smartphone with access to mobile internet, should speak German fluently and should not work in 24 h shift work. The supporting buddy of smokers in the intervention group receives an email with a link to a background questionnaire that checks for eligibility criteria, asks for informed consent, and contains instructions on how to use the app. Moreover, buddies are instructed to also fill out an end-of-day diary from 7 days before the quit date of the smokers, the quit date itself, and 20 days after (challenge diary phase). One day prior to the first diary day, smokers and buddies receive a reminder on how to connect and to use the SmokeFree Buddy app.

#### Control group

The participants in the control group will also announce a self-set quit date, measure the exhaled carbon monoxide daily using the iCO Smokerlyzer and fill out the end-of-day diary for 28 consecutive days during the diary phase. Smokers in the control group will, thus, have the same setting as the intervention group only without the SmokeFree Buddy app.

### Measures

#### Smokers in the intervention and control group

The prescreening questionnaire assesses inclusion and exclusion criteria as well as measures on socio-demographics and habitual smoking behavior adapted from Keller et al. [47]. At the background assessment smokers complete a comprehensive questionnaire on current smoking, smoking history, self-regulation (e.g., smoking-specific self-efficacy, action planning, action control) [48, 49], health status [50], personality and further potential control variables. Additionally, an objective baseline measure for smoking status is taken using the mobile iCO Smokerlyzer. All three end-of-day diary phases (baseline diary, challenge diary and follow-up diary) include short scales or single items on self-reported daily smoking abstinence, number of cigarettes smoked, quantity and quality of received social support from the buddy and from other network members [26, 31, 51], quantity and quality of received social control from the buddy and from other network members [52–54], self-regulation (e.g., self-efficacy, action planning, action control) [49], indicators of subjective well-being [55], relationship quality [56] and further potential control variables. Smokers in the control group do not receive items relating to the buddy. Smokers in the intervention group additionally report on the use of the SmokeFree Buddy app. On the first day of the follow-up diary, smokers are asked to report on their smoking abstinence and lapses since their self-set quit date. During both the 28-days challenge diary and the 3-day follow up diary, all participants measure their daily smoking behavior objectively with their personal mobile iCO Smokerlyzer.

#### Buddies of smokers in the intervention group

Buddies complete a combined prescreening and background questionnaire, assessing inclusion and exclusion criteria, socio-demographic variables, motivation to assist the smoker, health status [50], personality, and further control variables. They only participate in the 28-day challenge diary phase that contains relatively parallel items to the diary of the smokers assessing the buddies’ subjective well-being [55], quantity and quality of provided social support [26, 31, 51], quantity and quality of provided social control [53, 54], relationship quality [56], as well as their perspective on the smoker’s regulation during the quit attempt.

